### Outcomes {12}

Table 1 shows the outcomes and timeline of the study. The primary outcome will be the onset of T2D/confirmed by a 2-h 75 g oral glucose tolerance test (OGTT) over a 4-year study period. OGTT will be done at the screening visit, year 1 visit, and follow-up visits in years 2, 3, and 4. Secondary outcomes include (a) onset of impaired fasting glucose and impaired glucose tolerance; (b) changes in cardiometabolic variables (body weight, HbA_1c_, insulin, blood lipids, blood pressure), and (c) changes in women’s body composition as assessed by bioelectrical impedance analysis (BIA). Secondary measures will be taken at baseline visits, middle point, year 1, and 2, 3, and 4-year follow-up period.

**Table 1 Tab1:** Outcomes and timeline

Assessments	Screening visit	Baseline visit	Midpoint visit (26/27 weeks)	Year 1 visit	Year 2 visit (follow-up)	Year 3 visit (follow-up)	Year 4 visit (follow-up) endpoint
Lab tests							
OGTT test	X				X	X	X
Height, weight and blood pressure measurements	X	X	X	X	X	X	X
Bio-sample collection: buccal swab, saliva, and stool samples		X		X			X
BIA		X		X	X	X	X
Fasting blood draw		X	X	X	X	X	X
Questionnaires							
Demographics	X			X			
GDM and family history of diabetes	X						
Spouse and child health	X			X			
Lifestyle and dietary	X			X			
Diabetes awareness	X			X			
14-day e-Diary recording		X	X	X	X	X	X
SF-36		X	X	X	X	X	X
STAI		X	X	X	X	X	X
BDI-II		X	X	X	X	X	X
CERQ		X	X	X	X	X	X
MEQ		X	X	X	X	X	X
PSQI		X	X	X	X	X	X
SHS		X	X	X	X	X	X
HLQ		X	X	X	X	X	X
PSS-4		X	X	X	X	X	X
WHO-5		X	X	X	X	X	X
Child-related questionnaires							
BISQ-R-SF		X		X			
CSHQ		X		X			
StimQ toddler/preschool		X		X	X	X	X
ASQ-3		X		X	X	X	X
BRIEF-2		X		X	X	X	X
BASC-3-BESS Parent Form		X		X	X	X	X
Questionnaires administrated within the LvLUP App (intervention group only)							
PHQ-4		x	x				
IPAQ-SF		x	x				
MFFQ		x	x				

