## Assignment intervention: allocation

### Sequence generation {16a}

A total of 400 women will be stratified and randomised based on prognosis factors to either group 1 (intervention) or group 2 (control) based on 1:1 allocation using R statistical software.

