## Statistical methods

### Statistical methods for primary and secondary outcomes {20a}

#### Analysis of aggregate intervention effects

The primary continuous outcome for the onset of diabetes will be analyzed with linear mixed models (LMM) with outcome measurement (at the three follow-up time points) as the dependent variable and based on the intention-to-treatment (ITT) principle.

Multiple linear regressions will determine the relationship between outcome measures and predictors, adjusting for potential confounders. Multiple linear regression analyses will estimate the effects between groups at the end point follow-up. Generalised estimating equations and mixed effect models will be used for longitudinal data analysis. A *p*-value of < 0.05 will be considered statistically significant. Correction for multiple tests will be performed. All statistical analyses will be conducted using the R program or STATA for Windows (Stata Corporation). The treatment effect within and between the two groups will be assessed using the Cohen *d* statistics [65].

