### Interim analyses {21b}

Interim analyses will be conducted to examine initial trial efficacy and safety outcomes. Frequencies (percentages), means (standard deviations), or medians (interquartile ranges) will be used to summarise the data collected from questionnaires and surveys. Statistical tests will be performed, e.g. Chi-square or Fisher’s exact test for categorical variables, and two independent sample *t*-tests or ANOVA for continuous variables. Nonparametric tests will be used as deemed fit. For binary outcomes, the strength of associations between independent and dependent variables will be assessed by odds ratio estimated in logistic regression models. Crude associations will be evaluated using univariate models. Subsequently, associations will be evaluated using multivariable models adjusted for potential confounders.

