### Methods for additional analyses (e.g. subgroup analyses) {20b}

We will carry out additional analyses that evaluate the effect of the intervention on the children born to the women during the GDM pregnancy with a focus on cognitive and socio-emotional development (ASQ-3, BASC-3-BESS, BRIEF, StimQ) and sleep (BISQ-R-SF, CSHQ) using linear mixed models (LMM) with outcome measurements (baseline and the three follow-up time points) based on intention-to-treat (ITT).

Descriptive statistics will be used to establish the intervention response rate based on the number of coaching sessions completed, logins into the App, and estimated time spent.

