### Methods in analysis to handle protocol non-adherence and any statistical methods to handle missing data {20c}

Intention-to-treat analysis will be used to examine trial efficacy. Total scores will be modelled using fixed effects of time, intervention group, interaction between time and intervention group, and a random effect of individual.

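### Randomisation is stratified and baseline values are collected, but no stated between-arm model includes the strata or a baseline covariate, and the regression adjustment set is left open; the cost is precision

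*Protocol article*

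**What the plan says.** All references are to the protocol article.

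- **Sequence generation {16a}:** "A total of 400 women will be stratified and randomised based on prognosis factors", with 1:1 allocation. The factors are not named.
- **Outcomes {12}:** "Secondary measures will be taken at baseline visits, middle point, year 1, and 2, 3, and 4-year follow-up period". The OGTT is done at screening, and Table 1 places the women's questionnaires at the baseline visit.
- **Analysis of aggregate intervention effects {20a}:** the primary analysis uses "linear mixed models (LMM) with outcome measurement (at the three follow-up time points) as the dependent variable". Next comes a general regression sentence: "Multiple linear regressions will determine the relationship between outcome measures and predictors, adjusting for potential confounders". A further sentence says that multiple linear regression will estimate the between-group effect at the end point; it names no covariate.
- **Interim analyses {21b}:** crude models come first, then "associations will be evaluated using multivariable models adjusted for potential confounders". No list is given.
- **Additional analyses {20b}:** the mixed model for child outcomes explicitly has baseline among its response time points.
- **Non-adherence and missing data {20c}:** "Total scores will be modelled using fixed effects of time, intervention group, interaction between time and intervention group, and a random effect of individual". The section does not say whether baseline is a level of time.

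**The concern.** Stratifying the randomisation balances the arms on factors expected to predict outcome. That balance makes the treatment estimate less variable, but the model-based standard error reflects this only if the factors are in the model. If they are left out, the standard error is too large and the test rejects less often than its nominal level. A baseline measurement of a continuous outcome is usually its strongest single predictor, and here it is already collected. The stated models use neither as a covariate.

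The second issue is the open adjustment set. In a randomised comparison, covariates are chosen in advance for their prognostic value. An unlisted set of potential confounders can be settled after the data are seen. The article makes that a practical risk: participants and research personnel are not blinded {17a}, interim efficacy is examined {21b}, and data exports are prepared for monthly review and reported to the investigators {21a}.

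**Working it through.** **1. The plan's own sample size (Sample size {14}).** Inputs: hazard ratio 0.5, power 80%, control median 6 years, follow-up 3 years, 20% censoring. I take alpha as 5% two-sided; the printed 0.05% would need 156 events and cannot give the stated 65.

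- Events (Schoenfeld): 4(1.960 + 0.842)² / (ln 0.5)² = 65.35, against 65 stated. Power at 65 events is 0.798.
- Event probabilities, with event hazard λ = ln 2 / 6 in the comparison group (half that under intervention) and censoring hazard c = 0.2 per year: λ/(λ + c) × [1 − exp(−3(λ + c))] = 0.224 and 0.121, against 0.22 and 0.12 stated.
- N = 65 / [(0.224 + 0.121)/2] = 377.1 using unrounded probabilities, against 189 + 188 = 377 stated.

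The figures reproduce. They assume no covariate adjustment, so leaving covariates out does not change them.

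**2. Baseline covariate, continuous outcomes.** The article gives no correlation r between baseline and follow-up, so r is assumed and shown as a range. Large-sample variance of the arm contrast at one follow-up visit, relative to follow-up values alone:

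- follow-up only: 1
- baseline as a response level, time-by-group contrast: 2(1 − r)
- baseline as a covariate: 1 − r²

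| r | Follow-up only | Baseline as response | Baseline covariate | Cut vs follow-up only | Cut vs baseline as response |
|---|---|---|---|---|---|
| 0.3 | 1 | 1.40 | 0.91 | 9% | 35% |
| 0.5 | 1 | 1.00 | 0.75 | 25% | 25% |
| 0.6 | 1 | 0.80 | 0.64 | 36% | 20% |
| 0.7 | 1 | 0.60 | 0.51 | 49% | 15% |

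In power terms, take 188 per arm and a standardised effect of 0.289, which gives 80% power on follow-up values alone. At r = 0.5 / 0.6 / 0.7, baseline as a response gives 0.80 / 0.88 / 0.95 and baseline as a covariate gives 0.90 / 0.94 / 0.98.

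**3. Stratification factors.** The share R² of outcome variance that they explain is not given and is assumed. With strata balanced by design, a model without them overstates the standard error by 1/√(1 − R²). This was checked by simulation: 4,000 trials per setting, n = 376, two equal strata, exact balance, effect 0.29 SD. Monte Carlo error on a 5% rate is √(0.05 × 0.95 / 4000) = 0.003.

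| R² | SE ratio | Type I error, strata ignored | Type I error, strata included | Power, ignored | Power, included |
|---|---|---|---|---|---|
| 0.1 | 1.054 | 0.035 | 0.044 | 0.81 | 0.84 |
| 0.2 | 1.118 | 0.027 | 0.047 | 0.82 | 0.87 |
| 0.4 | 1.291 | 0.011 | 0.051 | 0.86 | 0.95 |

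The gains in steps 2 and 3 overlap, because a baseline value may carry much of what the strata explain. They should not be added.

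**The case against.** Five points can be made in defence.

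- **Baseline is not absent everywhere.** A reader might infer that it is. The child-outcome model in {20b} has it as a response, and time in {20c} may include it. This stands: the accurate statement is that no model has a baseline covariate. The {20a} model is different. It names only the three follow-up points, whereas {20b} adds baseline explicitly when it is meant.
- **The confounder wording is not part of the {20c} model.** A reader might infer that the article's treatment-effect model is adjusted for confounders in place of strata and baseline. The text does not say so. In {20a} the phrase belongs to a sentence about outcomes and predictors, and in {21b} to associations in interim analyses. The open list therefore matters only where those regressions are used to compare arms, so it is a secondary point.
- **Power is not short.** A reader might infer that a trial planned at 80% power drops below it. The event calculation is unadjusted. With 400 randomised, events scale to 65 × 400/377 = 69 and power to about 0.82. In the simulations, power with strata ignored stayed above 0.80. This stands.
- **The variance formulas suit continuous outcomes only.** This also stands. They do not apply to T2D onset, where no woman has diabetes at entry, nor to the logistic models in {21b}.
- **This is detail for an analysis plan.** It stands only in part. A list of covariates is often left to one, but {20c} writes the model term by term and {20a} and {21b} state an adjustment rule, so a plan that added the missing terms would depart from published text.

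**Conclusion.** The point holds as forgone precision in models that the article itself specifies. For continuous outcomes with r between 0.5 and 0.7, a baseline covariate would cut variance by 25% to 49% against a follow-up-only model. If baseline is already a response level, the cut is 25% falling to 15%. Leaving out strata that explain 10% to 20% of variance overstates the standard error by about 5% to 12%, brings the type I error to about 0.035 to 0.027, and costs about 3 to 5 points of power. Both r and R² are assumptions, and the R² range is the weaker one because the factors are unnamed.

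Neither bias nor an inflated type I error follows from these omissions, and the plan for 377 participants and 65 events is unaffected. The unlisted confounders are a separate, smaller weakness: the list might include the strata or baseline, but a reader cannot tell.

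**What to change.** 1. In {16a}, name the stratification factors.
2. Include them as fixed covariates in every between-arm model, including those in {20a}, {20b} and {20c}.
3. For each continuous outcome, add its baseline value as a covariate. Where baseline is kept as a response level, constrain baseline means to be equal across arms, which recovers essentially the same precision. State in {20c} which form is used.
4. In the model for T2D onset, include screening OGTT glucose, kept continuous, as a prespecified prognostic covariate.
5. In {20a} and {21b}, replace the reference to potential confounders with this fixed list for any comparison between arms. In {21b}, say whether the crude or the adjusted estimate is decisive.

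No new data are needed: the values come from the screening and baseline visits, and factors used to stratify must already be recorded at randomisation. The cost is wording, and the change should be made before further outcome data are examined by arm.

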### Plans to give access to the full protocol, participant-level data and statistical code {31c}

The anonymized datasets analysed during the current study and statistical code are available from the corresponding author on reasonable request, as is the full protocol.

## Oversight and monitoring

### Composition of the coordinating centre and trial steering committee {5d}

The study team will have overall responsibility for monitoring the integrity of the study and participant safety. The study team will monitor consent procedures, and safety plans prior to study initiation, amendments thereafter, and monitoring study progress, in terms of recruitment and retention of participants, adverse events, and protocol deviations.

### Composition of the data monitoring committee, its role and reporting structure {21a}

The committee comprises research coordinators (RCs), a data manager, co-investigators, and the principal investigator ([name]). RCs are responsible for electronic data capture following the standard operating procedure, and the data manager monitors data collection. The data manager will raise queries with RCs during data monitoring. The data manager prepares data exports for monthly review and reports to the principal investigator and co-investigators.

### Adverse event reporting and harms {22}

The Principal Investigator (PI) ([name]) will manage the data and safety monitoring after participant enrolment. In the event of any adverse events or safety issues, appropriate reporting will be made to DSRB accordingly. Regarding the questionnaires, we have the following monitoring plan: (a)BDI-II: participants who exhibit suicidality ideation (item 9) or have scored 29 or above (severe depression) will be offered a clinical referral. If the participant declines the referral, she will be provided with local helpline contact numbers (Samaritans of Singapore and Institute of Mental Health); (b) STAI: for participants who exhibit high anxiety with a score of 45 or above in the STAI, the study team will provide a local helpline contact number (Singapore Association for Mental Health). Additionally, the PHQ-4 will be completed by the LvL UP App participants (intervention group) with a score of 9 or higher (severe anxiety depression); the LvL UP App will provide information regarding mental health services in Singapore, including local helplines. The study team will follow up with the participant if she wishes to get a clinical referral. Finally, based on the ASQ-3, if a child shows scores suggesting developmental delay, we will discuss with the participant if she has any concerns and would like a referral for clinical follow-up.

Biological samples will be collected through blood tests, which will be analyzed by an accredited lab providing the normal reference range of the lab results. The PI ([name]) will review blood test results. For all abnormal blood test results and incidental findings discovered during the study period, the study PI will determine if the findings are clinically significant and actionable. The study PI will sign a referral letter to seek primary healthcare. Subsequently, a delegated study team member will contact the participant to relay the internal findings on behalf of the study PI. Participants who agree to be re-identified and notified of the internal findings will be contacted at their primary contact number provided in the consent form. The referral letter will be emailed to her. If the participant is uncontactable on her direct contact number, her next of kin listed on the consent form will be contacted. If the participant and next of kin are not contactable after 1 month, the referral letter will be sent directly to the participant’s home address. In the case incidental findings meet the study exclusion criteria, the affected participant will be informed and withdrawn from the study.

For the rest of the study measures/questionnaires, there is no clinical validation available. Hence no applicable management plan will be carried out.

### Frequency and plans for monitoring trial conduct {23}

Study activities, including those related to consent, randomisation, data collection, and intervention, will be monitored on an ongoing basis***.*** The data management team will monitor the data on the Amazon Web Services (AWS) server and REDCap platform. The study team will upload outcome data by the participants at the AWS server monthly.

### Plans for communicating necessary protocol amendments to relevant parties (e.g. trial participants, ethical committees) {25}

Changes to the study protocol will be communicated to the DSRB when required. Deviations from the protocol will be fully documented using a breach report form and it will be updated to the protocol in the clinical trial registry.

### Dissemination plans {31a}

Study results will be disseminated through webinars, written documents, conferences, and research meetings at SICS. We will also prepare scientific reports of the study results for publication in peer-reviewed journals.

## Discussion

This study aims to identify post-GDM women from community settings in Singapore and assess the effectiveness of a holistic lifestyle mHealth intervention for the prevention of T2D and CMDs. It is essential to develop preventative interventions to encourage healthy lifestyle habits, given the high incidence rates of T2D and CMD among women following GDM. This study may provide further support for the effectiveness of preventative interventions that consider the close relationship between physical and psychological health. Holistic lifestyle interventions that promote healthy habits such as maintaining a balanced healthier diet, engaging in regular physical activity, getting adequate sleep, and prioritising mental well-being can work together to produce more effective results [34, 66, 67]. mHealth also offers practical, affordable, and scalable intervention support for individuals adopting and maintaining healthy lifestyles. The evidence has shown that holistic mHealth targeting lifestyle behaviours are available and have shown to be effective [31, 34, 37]. However, few studies have been tested using multicompetent lifestyle using mHealth [34]. This RCT study represents a pioneer attempt to investigate the effectiveness of a holistic lifestyle mHealth intervention focused on the prevention of T2D and CMDs in women with a history of GDM.

mHealth has the potential to transform preventive healthcare, and particularly support post-GDM women who encounter challenges due to fatigue, child-caring responsibilities, and motivation to change their lifestyles. Additionally, we expect that the holistic mHealth proposed will permit to build capacities to disseminate interventions and could have enormous public health implications for the region and serve as a model for implementing preventative interventions in Asia and globally.

## Trial status

DSRB Approval of Protocol Version 1.0; 1/6/2023. Recruitment began 20/10/2023. Recruitment is tentatively scheduled to be completed on 30/10/2024.

## Data Availability

Final de-identified data and trial materials will be publicly available after the trial is concluded.

## Abbreviations

A*STAR: Agency for Science, Technology and Research
AWS: Amazon Web Services
BASC-3-BESS: Behavioral and Emotional Screening System
BCT: Behavioural change techniques
BISQ-R-SF: Brief Infant Sleep Questionnaire-Revised Short Form
BDI-II: Beck Depression Inventory
BRIEF-2: Behaviour Rating Inventory of Execute Functions-2
CBT: Cognitive behavioural therapy
CERQ: Cognitive Emotion Regulation Questionnaire
CMD: Common mental disorders
CSHQ: Children’s Sleep Habits Questionnaire
DSRB: Domain-Specific Review Board
DPP: Diabetes Prevention Program
HLQ: Health Literacy Questionnaire
GDM: Gestational diabetes mellitus
MEQ: Morningness-Eveningness Questionnaire
NUHS: National University Health System
NUS: National University of Singapore
PA: Physical activity
PHQ-4: Patient health questionnaire, 4-item
PI: Principal investigator
PSQI: The Pittsburgh Sleep Quality Index
PSS-4: Perceived Stress Scale 4
PP: Positive psychology
RCT: Randomised control trial
SEC: Singapore ETH-Centre
SHS: Subjective Happiness Scale
SICS: Singapore Institute for Clinical Sciences
SF-36: Short-form health curve
STAI: The State-Trait Anxiety Inventory
StimQ toddler/preschool: Cognitive Home Environment Questionnaire toddler/preschool
T2D: Type 2 diabetes
WHO-5 Wellbeing Index: World Health Organization-5 Wellbeing Index
